## Abstract

Physical literacy is crucial for children’s appropriate development and physical, social and mental health. In a school setting, class-based physical activity (PA) interventions are considered to be appropriate programs to foster PA participation and cognitive development. The purpose of this project, named the Active Learning in PHYsical Literacy (ALPHYL) study, was to describe a multicomponent classroom-based physically-active learning randomised control trial (RCT) in primary school children. The main purpose was to promote children’s physical literacy, academic achievement and cognitive function. The ALPHYL study is mainly based on physical literacy, active school models and the Supportive, Active, Autonomous, Fair and Enjoyable principles. The ALPHYL is an 8–10-week RCT to be conducted in six primary schools (12 classes) in Valencia (Spain) and its metropolitan area. Schools will be randomly assigned to the intervention or waiting-list control group. After a 30 h in-person training course for teachers and weekly meetings in the three months of resource preparation, the ALPHYL intervention will be conducted in physical education (PE) and non-PE lessons by teachers. The intervention consists of at least three daily sessions of physically active learning in addition to model-based PE teaching. Its feasibility will be evaluated weekly according to the Reach, Effectiveness, Adoption, Implementation and Maintenance framework. To assess its effectiveness, a pre-test, post-test and retention (8–10 weeks post-intervention) with primary outcomes (i.e., PA level, motor competence, perceived motor competence and PL, motivation, perceived social support, academic achievement and cognitive function), secondary outcomes and covariates will be collected.

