## 2. Materials and Methods

### 2.1. Study Design and Participants

The Active Learning in PHYsical Literacy (ALPHYL) study is a RCT in primary schools in Valencia (Spain) and its metropolitan area, with the schools as the units of randomisation and the students as the units of analysis. The design, implementation and reporting of ALPHYL will be carried out according to the CONSORT statement [25] and considering the SPIRIT recommendations. The sample will consist of at least 264 primary school Grade 5 pupils (i.e., 10–11 years old).

The sample size was calculated from previous studies that focused on the effects of interventions on PA and motor competence [11,22], using G*Power 3.1 software (University of Düsseldorf, Düsseldorf, Germany). From these studies, for an effect size between 0.30 and 0.32 with an alpha level of 0.05 and statistical power of 90%, the sample size had to be between 105 and 220 participants. To avoid reducing statistical power due to experimental mortality, the sample was increased by 20%, with the participation of 264 children. To recruit the participants, children from six schools (three intervention and three control schools; four public and two private) in Valencia and its metropolitan area will take part, consisting of pupils willing to participate and whose families provide signed informed consent (inclusion criterion). Pupils who present evident physical and mental difficulties that prevent them from satisfactorily completing all the measurements proposed in the study will not be included in the analyses (exclusion criteria). Only typically developing children will be included in the analysis.

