### 2.6. Data Management and Statistical Methods

To avoid possible bias in the data analysis, an independent blinded researcher will carry out a pseudonymisation process to guarantee the anonymity of the data. Missing data will be imputed using multiple imputation. According to our Institutional Review Board (IRB), a data monitoring committee will not be necessary since this is a low-risk study. Adverse events and protocol deviation will be documented by teachers using their personal teaching diary. Moreover, the research team will perform weekly audits to ensure data quality and the correct development of the protocol.

Independent researchers will also code actual motor competence videotapes so that they are stratified and counterbalanced. The video coded data, information from the individual questionnaires, accelerometer data and a family proxy-report of the participants’ residential neighbourhood will be hosted on an open access digital platform (zenodo.org) to be available to the scientific community.

The teachers’ data obtained in the semi-structured interviews will be categorised and thematically analysed by the NVivo^®^ qualitative analysis program (QSR International: Technology & Software Solutions, Burlington, MA, USA).

Structural equation modelling will be conducted to analyse the association and mediating role of some of the measured variables according to the conceptual models of children’s motor development and physical literacy [21,66]. To study the effect of the intervention on primary and secondary variables, linear mixed models will be built with the time, condition and interaction of time and condition as fixed effects, adjusting for baseline values. When a significant interaction effect is found, post-hoc tests will be applied by the least significant difference method. The data will be analysed on different statistical software, mainly SPSS (SPSS Inc., Chicago, IL, USA) and Mplus [67].

An analysis of the intervention effects in a person-centred approach will allow us to determine the children’s profiles according to their primary physical literacy outcomes (i.e., actual and perceived motor competence, motivation, perceived social support and cognitive function), while the trends and association will be analysed with the remaining physical literacy primary and secondary outcomes, for which self-organised maps will be created on MATLAB (MathWorks Inc., Natick, MA, USA).

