**Primary physical outcomes**		
Actual MC	Canadian Agility Movement Skill Assessment test (CAMSA)	[35,36]
PA level	ActiGraph wGT3X-BT (ActiGraph Corp, Pensacola, FL, USA, EEUU).	[37]

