**Primary psychological outcomes**		
Perceived MC and physical literacy	Pictorial scale of Perceived Movement Skill Competence (PMSC) and Physical Literacy for Children Questionnaire (PL-C Quest)	[38,39,40]
Self-determined motivation for PA	Adapted version for children of the Behavioural Regulation Exercise Questionnaire	[41,42]

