**Primary social outcomes**		
Perceived social support	The Physical Activity Family and Friends Support Scale (PASS)	[43,44]

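### Seven undifferentiated primary headings cover at least nine measures, with no familywise rule or decisive time point: if each is tested at 0.05, the false-positive risk reaches about 30% to 37%

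*Protocol article*

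**What the plan says.** - **Primary set.** The Abstract gives "primary outcomes (i.e., PA level, motor competence, perceived motor competence and PL, motivation, perceived social support, academic achievement and cognitive function". That is seven headings, none of them marked as the main one.
- **Measures.** Table 2 assigns the instruments. Two headings carry two each: perceived competence and physical literacy have the "Pictorial scale of Perceived Movement Skill Competence (PMSC) and Physical Literacy for Children Questionnaire (PL-C Quest"), and cognitive function has Stroop and Digit Span. The other five have one each: CAMSA, accelerometer, motivation questionnaire, PASS and final grades. No single score is named for the accelerometer, the motivation questionnaire or the grades, so nine is a minimum.
- **Analysis.** Section 2.6 applies one form of linear mixed model (time, condition, their interaction, baseline adjustment) to all primary and secondary variables. After a significant interaction, "post-hoc tests will be applied by the least significant difference method".
- **Times.** Outcomes are taken at pre-test, post-test and retention. Neither follow-up is given priority.
- **Significance level.** The article states 0.05 once, in the sample-size paragraph of section 2.1. That calculation draws on "previous studies that focused on the effects of interventions on PA and motor competence". Section 2.6 states no level.

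**The concern.** When several outcomes are all primary, the plan has to say what counts as success: all of them, one named outcome, or any of them after adjustment. This plan says none of these, and each outcome is judged by its own interaction test. Any one of nine or more measures, at either follow-up, could then be presented as a positive primary result. The 0.05 used for planning would not be the error rate of that claim.

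The rest of the article does not show which outcome should decide. The sample size rests on physical activity and motor competence, while the Abstract and Introduction give the main purpose as physical literacy, academic achievement and cognitive function.

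**Working it through.** **1. Count.** CAMSA (1), accelerometer (1), PMSC and PL-C Quest (2), motivation (1), PASS (1), grades (1), Stroop and Digit Span (2): 1 + 1 + 2 + 1 + 1 + 1 + 2 = 9 measures under 7 headings.

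**2. The plan's own figures.** The article states no familywise error rate, so only the sample size can be reproduced.
- 220 × 1.20 = 264, as stated.
- The lower figure of 105 is reproduced by a two-group F test with f = 0.32, numerator df 1, alpha 0.05 and power 90%.
- The upper figure of 220 does not follow from the stated inputs alone: f = 0.30 with df 1 gives 119. It is matched only with a numerator df of 8, which the article does not report.

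**3. Chance of at least one false-positive primary, all nulls true, each test at 0.05.** For m independent tests this is 1 − 0.95^m:
- m = 7: 1 − 0.95^7 = 0.302
- m = 9: 1 − 0.95^9 = 0.370

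The article gives no correlations between outcomes, so a range was assumed. Two-sided normal tests with equal pairwise correlation were simulated with 400,000 draws; the first row is the formula.

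| Assumed correlation | 7 tests | 9 tests |
|---|---|---|
| 0 | 30.2% | 37.0% |
| 0.1 | 29.8% | 36.4% |
| 0.3 | 27.1% | 32.6% |
| 0.5 | 23.0% | 26.9% |
| 0.7 | 17.8% | 20.2% |

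Counting only errors that favour the intervention, nine independent tests give 1 − 0.975^9 = 0.204. A chance above one half needs ln 0.5 / ln 0.95 = 13.5, so at least 14 independent tests.

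**4. Do the LSD comparisons add to this?** A claim needs a significant interaction first. Under the global null, gated claims for one outcome therefore cannot exceed the rate of the interaction test. A simulation (20,000 trials, 110 children per arm, three times, correlation over time 0.5 or 0.7, no clustering) took the between-arm differences in change to post-test and to retention:
- interaction significant: 4.9% and 5.0%
- either contrast significant, without the gate: 9.3% and 9.2%
- either contrast significant, behind the gate: 4.1% and 4.3%

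**5. Cost of adjustment.** Holm over nine measures starts at 0.05/9 = 0.0056. At that level Bonferroni gives 1 − (1 − 0.05/9)^9 = 0.049 for independent tests. On the F-test basis that reproduces 105:

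| f | N for 90% power at 0.05 | N at 0.0056 | N at 0.0056 plus 20% | Power at N = 220, 0.05 | Power at N = 220, 0.0056 |
|---|---|---|---|---|---|
| 0.32 | 105 | 165 | 198 | 0.997 | 0.973 |
| 0.30 | 119 | 187 | 225 | 0.993 | 0.949 |

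With only 105 children and f = 0.32, power would fall from 0.901 to 0.672. All these figures treat children as independent and make no allowance for randomisation by school.

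**The case against.** **Multiplicity may be settled in an unseen SAP.** This is the strongest objection. The article is condensed, and testing order and adjustment are often left to the SAP. It stands in part: an SAP could supply a familywise rule, and its absence here would not by itself be a fault. But naming the primary outcomes belongs to the protocol, and this one has fixed a list of seven equal headings with a claim triggered outcome by outcome. It also chose a post-hoc method and a trigger for it without limiting the number of primary claims.

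**Readings that go too far.** A reader might infer any of these, and the document does not support them:
- *That a false-positive primary result is likely.* The figures run from about 18% to 37%, all below one half, and assume that every null is true.
- *That the plan states 0.05 for each primary test.* That level is given for the sample size only. Applying it to the outcome tests is an inference, though it is the only level in the article.
- *That unadjusted LSD contrasts at two follow-ups raise the error further.* The gate prevents this under the global null. For between-arm contrasts of change at the two follow-ups, LSD behind the joint interaction test acts much like a closed procedure within one outcome.
- *That physical activity and CAMSA must be the only confirmatory outcomes because the sample size rests on them.* This would demote academic achievement and cognitive function, both named in the main purpose, and the psychological and social parts of physical literacy.

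**Conclusion.** The concern holds as a badly fixed primary set. At least nine measures share primary status, each can yield a claim from its own interaction test, and neither a familywise rule nor a decisive time point is given. If each is tested at 0.05, the chance of at least one false-positive primary result when no effect exists is up to 30% (seven tests) or 37% (nine), and about 23% to 27% at an assumed correlation of 0.5. The upper figure is roughly seven times nominal.

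The size rests on three assumptions: 0.05 applies to each test, each heading or instrument gives exactly one score, and each test keeps its nominal level. More scores per instrument would raise it and stronger correlation would lower it. Whether the tests keep their level with three schools per arm is a separate matter. The LSD step matters only because it leaves open whether post-test or retention carries the claim.

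**What to change.** 1. Name one score for each primary measure, including the accelerometer metric, the motivation score and the grade record to be used.
2. Name post-test as the decisive time point. The hypothesis for each measure is then the between-arm contrast at post-test from the mixed model; retention is supportive.
3. Apply Holm to the nine resulting p-values at a familywise 0.05.

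Alternatively, the sponsor may pre-specify a smaller confirmatory set consistent with its stated purpose, apply Holm within it, and report the remaining measures with confidence intervals and no confirmatory claim. That choice should be dated before anyone sees outcomes by arm. If that moment has passed, Holm across all nine is the safer route, because it selects no outcomes.

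**Cost.** No new data are needed. The changes are to the wording of section 2.6, Table 2 and the SAP; narrowing the set may also require an update of the trial registration. The strictest threshold becomes 0.0056 for nine measures, with some loss of power per outcome. On the plan's individual-level basis the required numbers (198 to 225 with the 20% allowance) stay below 264, but clustering by school would reduce that margin.

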## 1. Introduction

Active play and physical activity (PA) during childhood favours cognitive, social and physical development and affects children’s present and future health [1,2]. Despite its benefits, the percentage of children who comply with the recommendation to perform at least 60 min of moderate-vigorous PA daily is alarmingly low [3,4]. In order to promote compliance with the recommendations, schools have been proposed as ideal settings for promoting active play, PA and reducing sedentary behaviour [5] while stimulating cognitive function [6]. In fact, pupils spend a large proportion of their time (around 7–8 h per day) at school [7]. PA during school hours is associated with aspects such as concentration, cognitive function and academic achievement [8,9,10], even though children remain seated for around 70% of the time in class [8,11,12]. School time could well be the least active and most sedentary period of the day [13]. Given the alarmingly low level of PA practice among young people in developed countries, 30 min of PA at school would contribute to improving their physical, cognitive and mental health [11,14]. If 10 min of sedentary time can be transformed into moderate-vigorous PA (MVPA), positive physical and psychological effects would be evident (e.g., increased motor competence and an improved self-concept) [15]. Implementing interventions that increase school PA levels (e.g., physically active learning) may well be an ideal and low-cost method to improve students’ health and academic achievement [16].

In the educational setting, physical education (PE) can be a favourable context for promoting PA within and outside school hours [5,17]. However, in primary schools, little time is dedicated to PE (7–10% of the weekly timetable) and PE sessions do not always involve MVPA, so the chance to achieve pedagogical goals, such as promoting PA and motor competence, is limited [18,19]. Beyond the PE area, the involvement in subjects like maths, science or languages can provide a significant stimulus to increase the time spent in PA, reduce sedentary time and motivate interest in active lifestyles [5,14]. The implementation of physically active learning, both in PE and other subjects, has the potential to not only improve students’ PA levels during school hours [5], but also increase learning facilitators such as concentration, cognition and time-on-task, as well as executive functions and academic achievement [14]. All of this can be achieved without reducing instructional time in the different areas both in and out of the classroom [11]. To enhance cognitive performance, it seems that more than 20 min daily of MVPA in a physically active classroom is required [20]. So, to improve the PA levels and cognitive function, physically active classroom-based interventions should involve: (a) a length of up to 8–10 weeks and (b) a dosage of about 20–30 min, including 15–20 min of MVPA and another 10–15 min of light PA in which there is mainly cognitive involvement, respectively [11,13].

It is now recognised that the school context is central to the development of students’ physical literacy, which is understood as the motivation, confidence, physical competence, knowledge and understanding of valuing and taking responsibility for performing PA throughout life [21,22,23]. Beyond the mere physical connotation, physical literacy integrates the interrelated physical, psychological, social and cognitive dimensions. It should also be understood as a dynamic and individual construct, which is not acquired on an ad hoc basis, but involves a learning process influenced by the family, school and social environment [21]. Most recent studies have focused on increasing the volume of individuals’ PA, although the impact on qualitative aspects has not received as much attention [24]. It is thus recommended that school interventions should aim at the holistic improvement of students, in addition to maintaining a multicomponent structure (e.g., involving PE and other subjects, families, etc.). In this line, as opposed to approaches whose exclusive aim is to increase the volume of PA, physical literacy seeks to develop knowledge and understanding of how, why and when people move, and the social skills to be active with others [21,24]. However, so far, no multicomponent interventions based on physically active learning have been developed in areas other than PE that would allow us to know whether physically active learning leads to benefits, not only in the volume of PA practice, but also in other health aspects (e.g., enjoyment, social identity, weight status, etc.) and academic achievement. This study thus proposes the development of a multicomponent classroom-based physically active learning randomised control trial (RCT) in primary school children. The main purpose is to empower children’s physical literacy, academic achievement and cognitive function. The physical characteristics of the school and family environments will also be assessed in relation to PA practice and physical literacy during the intervention, which will be based on the theoretical model of creating active schools [14] and physical literacy [21].

## 2. Materials and Methods

### 2.1. Study Design and Participants

The Active Learning in PHYsical Literacy (ALPHYL) study is a RCT in primary schools in Valencia (Spain) and its metropolitan area, with the schools as the units of randomisation and the students as the units of analysis. The design, implementation and reporting of ALPHYL will be carried out according to the CONSORT statement [25] and considering the SPIRIT recommendations. The sample will consist of at least 264 primary school Grade 5 pupils (i.e., 10–11 years old).

The sample size was calculated from previous studies that focused on the effects of interventions on PA and motor competence [11,22], using G*Power 3.1 software (University of Düsseldorf, Düsseldorf, Germany). From these studies, for an effect size between 0.30 and 0.32 with an alpha level of 0.05 and statistical power of 90%, the sample size had to be between 105 and 220 participants. To avoid reducing statistical power due to experimental mortality, the sample was increased by 20%, with the participation of 264 children. To recruit the participants, children from six schools (three intervention and three control schools; four public and two private) in Valencia and its metropolitan area will take part, consisting of pupils willing to participate and whose families provide signed informed consent (inclusion criterion). Pupils who present evident physical and mental difficulties that prevent them from satisfactorily completing all the measurements proposed in the study will not be included in the analyses (exclusion criteria). Only typically developing children will be included in the analysis.

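### Schools are randomised, but no stated element of the design, sample size or effect model accounts for clustering by school or class; run as written, the baseline-adjusted condition test is anti-conservative

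*Protocol article*

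**What the plan says.** Section 2.1 describes the trial "with the schools as the units of randomisation and the students as the units of analysis". The Abstract gives "six primary schools (12 classes) in Valencia (Spain) and its metropolitan area", and section 2.1 splits the schools as "three intervention and three control schools; four public and two private". Section 2.3 confirms that the six schools are allocated three to each arm.

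For primary and secondary outcomes, section 2.6 states that "linear mixed models will be built with the time, condition and interaction of time and condition as fixed effects, adjusting for baseline values". A significant interaction then opens post-hoc comparisons by the least significant difference method. No random effect of any kind is named, whether for school, class or pupil. There is also no ICC, cluster-robust standard error or small-sample degrees-of-freedom method. School characteristics appear only as covariates to be measured (section on covariates, Table 3).

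The sample size in section 2.1 was obtained "using G*Power 3.1 software" for an effect size of 0.30 to 0.32, alpha 0.05 and 90% power: "the sample size had to be between 105 and 220 participants". After that, "the sample was increased by 20%, with the participation of 264 children". The 20% is for attrition only.

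**The concern.** Condition varies only between schools. Its sampling error therefore contains the variation between six schools, which leaves 6 − 2 = 4 degrees of freedom once the two arm means are estimated. A model that treats about 260 pupils as independent, given condition and baseline, takes its error from the wrong level.

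Clustering is plausible here. Each school's own teachers deliver the intervention, control PE teachers run their own programme, and academic achievement is taken from final grades. If school is left out, intervals and p-values for the baseline-adjusted effects are too optimistic on every outcome with positive school variance. A difference among six schools then has a raised chance of being declared an intervention effect.

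**Working it through.** **Inputs from the protocol.** 264 pupils, 6 schools, 3 v 3, alpha 0.05 (two-sided assumed). Average school size m = 264/6 = 44. The protocol gives no ICC. I assume 0.01, 0.05 and 0.10 for the baseline-adjusted outcome.

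**The plan's own figure.** A two-group ANOVA on independent pupils with f = 0.32, alpha 0.05 and 90% power needs 105, the lower stated number. The upper number, 220, does not follow from 0.30: f = 0.30 gives 119, and d = 0.30 gives 470 two-sided. The step 220 × 1.20 = 264 is correct as multiplication. That 220 cannot be reproduced is a separate matter. What counts here is that the figure that does reproduce assumes independent pupils, and that no design effect was applied.

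**Type I error of a pupil-level condition test without a school term.** Design effect DE = 1 + (m − 1) × ICC = 1 + 43 × ICC. Standard errors are too small by a factor √DE. True type I error = 2 × [1 − Φ(1.96/√DE)]. Effective sample size = 264/DE.

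| Assumed ICC | DE | √DE | True type I error | Effective N |
|---|---|---|---|---|
| 0.01 | 1.43 | 1.20 | 0.101 | 185 |
| 0.05 | 3.15 | 1.77 | 0.269 | 84 |
| 0.10 | 5.30 | 2.30 | 0.395 | 50 |

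A simulation of 20,000 null trials (6 schools of 44 pupils) gave 0.101, 0.275 and 0.402 for the pupil-level test. A t-test on the six school means (4 df) gave 0.051, 0.047 and 0.052.

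**Time-by-condition test.** This depends on a further unknown: the share of school variance that changes between time points. The simulations used 4,000 null trials per setting, three time points, a pupil random intercept and no school term, with half of the within-school variance lying between pupils. ICC here is total school variance over total variance.

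| Share of school variance that changes over time | ICC 0.01 | ICC 0.05 | ICC 0.10 |
|---|---|---|---|
| None | about 5% | about 5% | about 5% |
| One tenth | about 7% | about 13% | about 21% |
| One half | about 12% | about 39% | about 57% |

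If baseline enters as a covariate, only post-test and retention remain as outcomes and the interaction has 1 df. With a half share the rates are then about 11%, 27% and 41%.

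Stable school effects do not protect the baseline-adjusted comparison. With school effects constant over time and a raw ICC of 0.10 or 0.20, a pure change test kept its level (0.046 and 0.050), but analysis of covariance at pupil level rejected in 0.16 and 0.25 of null trials.

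**Power of a valid analysis.** For a school-level t-test on 4 df (critical value 2.776), the noncentrality is d/√(4 × DE/264).

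- d = 0.30, ICC 0.01: 0.30/0.1472 = 2.04, power 0.35.
- d = 0.30, ICC 0.05: 0.30/0.2185 = 1.37, power 0.19.
- d = 0.64 (the equivalent of f = 0.32): power 0.89, 0.60 and 0.41 at ICC 0.01, 0.05 and 0.10.

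The protocol does not say whether its effect size is d or f, so both are shown.

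**The case against.** The strongest reply is that the protocol is silent rather than wrong. It calls the models linear mixed models and lists their fixed effects. A school intercept would be a random effect and would not appear in that list, and a fuller analysis plan may contain one. This stands, and it makes the inflation conditional on the school term being absent. The same silence cuts the other way: a reader might infer that repeated measures within pupil are at least handled, but no pupil random effect is named either.

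A reader might also infer that naming pupils as the units of analysis is an error in itself. It is not. A pupil-level model is a proper analysis of a school-randomised trial once school is in the error structure.

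A third tempting inference is that the interaction test must be badly inflated. The documents do not support that. The test holds about 5% if school effects are stable, and the high rates above need a large share of school variance to change over time, which the protocol neither states nor excludes.

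The objection does not dispose of the point. The named unit of analysis, the listed model terms and a sample size without a design effect all point the same way, and nothing in the article points to an allowance for clustering. Even a plain school intercept would be inadequate with three schools per arm unless small-sample degrees of freedom were used.

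**Conclusion.** The point holds in conditional form. That no stated element handles clustering is certain from the text. If the model is run without a school term, the baseline-adjusted condition effect has standard errors too small by a factor of about 1.20, 1.77 or 2.30, and a true type I error of about 10%, 27% or 40%, at assumed ICCs of 0.01, 0.05 and 0.10 with 44 pupils per school. Even the smallest of these ICCs doubles the nominal error. For the time-by-condition test, which opens the post-hoc comparisons, the inflation runs from none to substantial according to how far school effects change over time. The protocol does not show that the final analysis will omit school; it gives no assurance that it will not. The correction bears on every effect estimate, so it should be made before the data are analysed.

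**What to change.** In section 2.6, choose one of two methods in advance.

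1. **Pupil-level mixed models.** Include school in the error structure, class within school where estimable, and school-by-time for the interaction. Test the condition and time-by-condition contrasts on small-sample degrees of freedom (Kenward-Roger or Satterthwaite, about 4). With 6 schools and 12 classes these variances will be poorly estimated, so state beforehand which terms are kept.
2. **One school-level analysis.** Use a t-test on 4 df of the six baseline-adjusted school means at each time point.

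The choice should not depend on whether the school variance is estimated as zero. At ICC 0.01 that would happen in about 40% of trials, and the data would then pick the method. A permutation test is no way out: 3 v 3 has 20 allocations, so the smallest two-sided p is 2/20 = 0.10.

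In section 2.1, amend the sentence on units to say that pupils are analysed with clustering by school accounted for, and do not claim 90% power for this analysis.

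The cost is wording and a little model code, with no new data. The real price is wider intervals and the lower power shown in the working, which should be stated openly.

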### 2.3. Procedure

The CONSORT study flow diagram is shown in Figure 1. A list of primary schools in Valencia and its metropolitan area will be obtained from the government educational institutions. The schools will be randomly selected and ordered in a list using computer-generated random numbers by a researcher from the study team. The inclusion criteria for the schools’ participations will be: (a) must have at least two groups of primary school Grade 5 pupils, and the teachers involved in both must agree to participate; (b) each class group includes at least 75% of the participants; and (c) children must not have taken part in other PA promotion interventions during the intervention period in the previous two years. If a school decides not to participate, the same procedure will be performed with the next school selected from the list. The six selected schools will also be randomly allocated to the intervention (*n* = 3) or control groups (*n* = 3). Students will be unaware of whether they have been allocated to the intervention or control group.

In order to detect barriers to and facilitators of the intervention’s adoption, implementation and sustainability, an instrument based on the reach, effectiveness, adoption, implementation and maintenance (RE-AIM) tool will be used to analyse its reach, effectiveness, adoption, implementation and maintenance [26], as well as its impact [8,26]. This instrument will be implemented with the teachers involved in the intervention, who will provide information on their teaching methods and the pupils’ participation by completing a personal teaching diary [13,27].

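### The 90% power comes from a calculation for individually randomised pupils, but only six schools are randomised

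*Protocol article*

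**What the plan says.** Section 2.1 of the protocol article describes a trial "with the schools as the units of randomisation and the students as the units of analysis". Section 2.3 confirms the number of units: "The six selected schools will also be randomly allocated to the intervention" arm (three) or the control arm (three). The Abstract gives the same structure, a trial "to be conducted in six primary schools (12 classes) in Valencia (Spain) and its metropolitan area".

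The sample size is also in Section 2.1. It was obtained "using G*Power 3.1 software", "for an effect size between 0.30 and 0.32 with an alpha level of 0.05", and the result was that for "statistical power of 90%, the sample size had to be between 105 and 220 participants". The only later adjustment is for drop-out: "the sample was increased by 20%, with the participation of 264 children".

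The paragraph gives no ICC, no design effect, no cluster size and no reason why six schools suffice. It also does not say whether 0.30–0.32 is Cohen's d, Cohen's f or something else.

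**The concern.** When schools are randomised, pupils in the same school share teachers, timetable and mode of delivery, and their outcomes are correlated. The information on the arm comparison then depends mainly on the number of schools. Two things reduce power relative to individual randomisation: the variance is inflated by the design effect, and the comparison rests on six school-level units, which leaves 6 − 2 = 4 degrees of freedom. Neither enters the calculation.

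The risk is in interpretation. With 90% power stated without qualification, a non-significant result invites the reading that a well-powered trial found no effect, when the school-level comparison may have had little chance of detecting one.

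**Working it through.** **1. Reproduce the plan's figures (individual randomisation, alpha 0.05 two-sided, 90% power).**
- Two-group F test, f = 0.32: total N = 105. This matches the stated lower bound exactly and contains no clustering term.
- Two-group F test, f = 0.30: N = 119, not 220.
- Two-group comparison, d = 0.32 and 0.30: N = 414 and 470, about twice the stated maximum.
- Drop-out: 220 × 1.20 = 264. This closes exactly, so no design effect can be hidden between 220 and 264.

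The lower bound therefore points to Cohen's f. The upper bound of 220, from which 264 is built, does not reproduce for a two-arm comparison under either metric, so d cannot be excluded.

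**2. Inputs for the cluster calculation.** From the article: 6 schools (3 v 3), 264 pupils, effect 0.30–0.32, alpha 0.05. Assumed: ICC 0.01, 0.05 or 0.10; equal school sizes; two-sided test. Under the f reading, d = 2f = 0.60–0.64.

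**3. Formulas.**
- m = 264 / 6 = 44
- Design effect DE = 1 + (m − 1) × ICC = 1 + 43 × ICC
- Effective N = 264 / DE
- SE(d) = 2 / √264 × √DE = 0.1231 × √DE
- Power from the noncentral t with 4 df, noncentrality d / SE, critical value 2.776
- Effect detectable with 90% power: about 4.40 × SE, since a noncentrality of about 4.40 gives 90% power on 4 df

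**4. Results with all 264 pupils retained.**

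| ICC (assumed) | DE | Effective N | SE(d) | Power, f reading (d 0.60–0.64) | Power, d reading (0.30–0.32) | Detectable d at 90% |
|---|---|---|---|---|---|---|
| 0.01 | 1.43 | 185 | 0.147 | 86–89% | 35–38% | 0.65 |
| 0.05 | 3.15 | 84 | 0.218 | 55–60% | 19–21% | 0.96 |
| 0.10 | 5.30 | 50 | 0.283 | 37–41% | 13–14% | 1.25 |

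**5. Results with 220 completers, the number left after the plan's own drop-out allowance (36.7 per school).**
- f = 0.30: 91% at ICC 0, below 90% once the ICC exceeds about 0.001, then 81%, 53% and 36% at ICC 0.01, 0.05 and 0.10.
- f = 0.32: below 90% once the ICC exceeds about 0.005.
- d = 0.30–0.32: 40–44% even at ICC 0, from the 4 df alone.

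**6. Effect of baseline adjustment.** Section 2.6 plans to adjust for baseline values. Multiplying the variance by (1 − r²), with the baseline correlation r assumed, gives these powers for the f reading:

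| Pupils | r (assumed) | ICC 0.01 | ICC 0.05 | ICC 0.10 |
|---|---|---|---|---|
| 264 | 0.5 | 93–96% | 67–72% | 46–51% |
| 220 | 0.5 | 90–93% | 64–69% | 45–50% |
| 220 | 0.7 | 97–99% | 80–84% | 60–65% |

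Under the d reading with 264 pupils, even r = 0.7 gives only 73–78% at ICC 0.

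**The case against.** The strongest reply is that the shortfall is conditional. The ICC and the metric are both assumed here. The match at 105 favours Cohen's f, and the d figures fit poorly with an N of at most 220. Under the f reading at ICC 0.01, unadjusted power with 264 pupils is 86–89%, close to the claim. With baseline adjustment at r = 0.5–0.7 and 220 completers, 90% holds up to an ICC of about 0.010–0.036. The fuller plan may also specify a school random effect and another degrees-of-freedom method, and nothing in the article says that a null result will be read as no effect.

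Much of this stands as a matter of emphasis. The f reading deserves more weight, the loss is not certain for every outcome, and the misreading of a null result is a risk, not a stated intention. It does not rescue the statement. The sample-size paragraph claims no baseline gain, and at ICC 0.05 power is still only 64–84% under that favourable case. Nor can a later analysis plan turn 264 into the product of a cluster calculation: a correct school term in the model would only bring the loss of power into the analysis.

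**Conclusion.** The concern holds. The stated 90% belongs to a design with independently randomised pupils, and the paragraph leaves no room for a hidden allowance for clustering. Under the more plausible f reading, unadjusted power with all 264 pupils falls from 86–89% at ICC 0.01 to 37–41% at ICC 0.10. Under the d reading it does not reach 90% at any ICC. These sizes rest on an assumed ICC range, equal school sizes and a two-sided test on 4 df. With three schools per arm, adding pupils helps little: at ICC 0.05 and unlimited pupils per school, power is still only about 69% for f = 0.30 and 25% for d = 0.30.

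**What to change.** Withdraw the 90% statement and rewrite the sample-size paragraph of Section 2.1 for the design actually randomised. It should give:
- the effect-size metric, the primary outcome it refers to, and how 220 was obtained;
- the assumed school-level ICC, its source and a range;
- the design effect 1 + (m − 1) × ICC with m = 44, and a test on 4 df, or another stated method suited to six clusters;
- any baseline correlation relied on, with its source;
- the resulting power, or the effect detectable with 90% power, for 6 schools and 264 pupils, and preferably also for 220 completers.

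Add a sentence that non-significant results will be interpreted from confidence intervals and not as evidence of no effect.

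The cost is a change of text and a less favourable stated power. No additional schools or pupils are asked for.
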